### Participant timeline

Members of the research team will provide a full verbal explanation and written description of the trial to women who meet the inclusion criteria (box 2 and 3). The woman will be given sufficient time to consider the information, and to decide whether she will participate in the trial. Written informed consent will be sought from the woman and taken by an appropriately trained healthcare professional. Eligibility will be assessed and baseline data, including all demographics, maternal demographics and patient questionnaires (completed by the woman), will be entered on a web-based database by members of the research team. Participants will be randomised and instructed in the use of self-monitoring and provided with a BP monitor or instructed to follow usual care. Women randomised to usual care will not be prevented from self-monitoring although we will ask all women at final follow-up if they have self-monitored during the trial. Participants on both arms will follow their routine care clinic visits until delivery. Participants will be contacted at around 30 weeks gestation (2 weeks after baseline if participants were recruited after 30 weeks) and asked either in person/over the phone/by post/or via email to complete patient questionnaires. The remainder of antenatal care, in particular the timing and mode of delivery, will be left to the discretion of the responsible clinician. A medical notes review will be undertaken following the primary discharge for mother and baby. If a woman and/or her baby is still in hospital at 2 months from delivery or 2 months from her estimated date of delivery (whichever is longer), the admission time will be censored and data collected up to that point. Self-monitoring of BP will finish at admission in established labour or the end of pregnancy, whichever is sooner and participants will continue with standard postnatal care. Participants will be contacted at around 8 weeks postdelivery and asked either in person/over the phone/by post/or via email to complete patient questionnaires and arrange for collection of the loaned BP monitor if not returned at delivery. A schedule of participant enrolment, interventions and assessments in the trial is shown in table 1 and a flowchart of study visits is shown in figures 4 and 5.

Box 2Blood pressure during higher risk pregnancy (BUMP 1) inclusion and exclusion criteriaInclusion criteriaParticipant is willing and able to give informed consent for participation in the trial.Pregnant woman, aged 18 years or above between 16+^0^ and 24+^0^ weeks.Able and willing to comply with trial requirements.Willing to allow her general practitioner and consultant, if appropriate, to be notified of participation in the trial.At higher risk for hypertension in pregnancy/pre-eclampsia defined as one or more of the following risk factors:Age 40 years or older.Nulliparity.Pregnancy interval of more than 10 years.Family history of pre-eclampsia.Previous history of pre-eclampsia or gestational hypertension.Body mass index 30 kg/m^2^ or above at booking.Chronic kidney disease.Twin pregnancy.Prepregnancy diabetes (type 1 or 2)Autoimmune disease (eg, systemic lupus erythematosus or antiphospholipid disease).Exclusion criteriaChronic hypertension.

Box 3Blood pressure (BP) during hypertensive pregnancy inclusion and exclusion criteriaInclusion criteriaWomen with chronic hypertension (defined as sustained systolic BP ≥140 mm Hg and/or diastolic BP ≥90 mm Hg, present at booking or before 20 weeks gestation, or receiving antihypertensive treatment outside pregnancy and/or at time of referral), recruited up to 37+^0^ weeks gestation.ORWomen with gestational hypertension after 20 weeks gestation (defined as sustained systolic BP ≥140 mm Hg and/or diastolic BP ≥90 mm Hg), recruited at 20+^0^ to 37+^0^ weeks gestation.ANDParticipant is willing and able to give informed consent for participation in the trial.Woman aged 18 years or above.Willing to allow her general practitioner and consultant, if appropriate, to be notified of participation.Exclusion criteriaAnticipated inpatient admission considered likely to lead to imminent delivery (within the next 48 hours).

**Table 1 T1:** Schedule of interventions and assessments

	Study period (16 weeks to 8 weeks postdelivery)			
Study visit	Trial entry/baseline	Antenatal follow-up	Notes review	Postnatal follow-up
Time point	20±4 weeks gestation	30±3 weeks gestation	40+4 weeks (postdelivery)	40+8 weeks (postdelivery)
Informed consent	X			
Eligibility assessment	X			
Demographics; including age, race, education	X			
Maternal demographics; including gestation, EDD and parity	X			
Patient Questionnaires; including EQ-5D-5L and STAI	X	X		X
Randomisation	X			
Recording home BP	Self-Monitoring group will record and submit reading between baseline and delivery			
Recording clinic BPs			X	
Maternal and perinatal outcomes			X	
Secondary outcome data			X	
Return of BP monitor			BP monitors will be returned at/or postdelivery	

BP, blood pressure; EDD, Estimated Delivery Date; EQ-5D-5L, EuroQoL 5 Dimensions 5 Levels; STAI, State-Trait Anxiety Inventory.

**Figure 4 F4:**
[figure not shown]
BUMP 1 study visit chart. BP, blood pressure; BUMP 1, BP during higher risk pregnancy.

**Figure 5 F5:**
[figure not shown]
BUMP 2 study visit chart. BP, blood pressure; BUMP 2, BP during hypertensive pregnancy.

### Sample size considerations

#### BP during higher risk pregnancies

The sample size was determined using a two-stage simulation process, which modelled how many women would be expected to develop hypertension and how long time to detection would take in these women, using data from our pilot work in the BUMP study. Assuming 16% of women develop hypertension, and an SD of 40 days to detection of raised BP in both groups, a sample size of 2262 (1131 per group) will allow detection of an effect size of 12 day’s difference in time to detection of raised BP in pregnancy between self-monitoring and control groups (the primary outcome of BUMP 1), with 90% power and 5% level of significance (two sided) and assuming a 15% attrition rate. If the SD is 45 days, then this sample size will allow detection of a difference of 14 days with more than 90% power and if the SD is 50 days then it will be sufficient to detect a difference of 16 days in time to detection of raised BP in pregnancy also with 90% power. Of the 2262 women recruited to BUMP 1, around 362 women are expected to develop hypertension. We will recruit a minimum of 2262 women to ensure adequate power. The simulation was carried out using R V.3.1.2. (https://www.r-project.org/).

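### BUMP 1: the stated 90% power for a 12-day difference cannot be reproduced from the printed inputs by comparing mean days; that reading gives about 75% after attrition

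*Protocol article*

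**What the plan says.** The Protocol article, under Sample size considerations, BP during higher risk pregnancies, describes a two-stage simulation in R based on pilot data. The first stage models how many women become hypertensive. The second models how long detection takes in those women.

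The inputs are "Assuming 16% of women develop hypertension, and an SD of 40 days to detection of raised BP in both groups". The result is that "a sample size of 2262 (1131 per group) will allow detection of an effect size of 12 day’s difference" "with 90% power and 5% level of significance (two sided) and assuming a 15% attrition rate".

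Two fallback scenarios follow for the same sample size. The first reads "If the SD is 45 days, then this sample size will allow detection of a difference of 14 days with more than 90% power". The second claims 90% power for 16 days if the SD is 50 days. The section adds: "Of the 2262 women recruited to BUMP 1, around 362 women are expected to develop hypertension".

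Under Statistical analysis, BP during higher risk pregnancy, the primary analysis is a two-part model such as a hurdle model. The article does not give the mean time to detection, the distribution of times, or the test used in the simulation.

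**The concern.** The effect and its SD are both stated in days, so a reader will take the claim as one about a difference in mean days among women who become hypertensive. On that reading a colleague can check the figure in a few lines, and it does not come out. The gap is not rounding: all three scenarios fall short of 90%, even with attrition ignored.

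This is the primary outcome of BUMP 1, and 2262 is presented as the minimum that secures adequate power. If the comparison-of-means reading is the right one, the chance of missing a true 12-day difference is about 25% rather than 10%. A null result would then be read as stronger evidence against a 12-day benefit than the design supports.

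**Working it through.** **Inputs**, all from the BUMP 1 sample size section: 1131 per group; 16% hypertensive; SD 40, 45 or 50 days in both groups; differences of 12, 14 or 16 days; two-sided 5%; 15% attrition; claimed power 90%, more than 90%, and 90%.

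**Step 1. The plan's own count.** 0.16 × 2262 = 361.9, which reproduces the stated 362. It is the number expected among women recruited, before attrition.

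**Step 2. Women with a time to detection, per group.**
- No attrition: 1131 × 0.16 = 181.0
- 15% attrition: 1131 × 0.16 × 0.85 = 153.8 (about 308 in all)

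**Step 3. Power for a difference in means.** Power = Φ(d·√(n/2) − 1.96), with d = difference/SD.
- 12 days, SD 40, no attrition: 0.300 × √(181.0/2) = 2.854; Φ(0.894) = 81.4%
- 12 days, SD 40, after attrition: 0.300 × √(153.8/2) = 2.631; Φ(0.671) = 74.9%

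| Scenario | d | Stated power | No attrition | 15% attrition |
|---|---|---|---|---|
| 12 days, SD 40 | 0.300 | 90% | 81.4% | 74.9% |
| 14 days, SD 45 | 0.311 | more than 90% | 84.1% | 77.9% |
| 16 days, SD 50 | 0.320 | 90% | 86.1% | 80.1% |

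For a comparison of means at one sample size, power rises with d. The stated sequence puts the middle scenario above the last. Rounding could hide a small rise, so this is only a supporting sign.

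**Step 4. What 90% would take.** n per group = 2 × (1.96 + 1.2816)² × (SD/difference)². For 12 days and SD 40 this is 233.5, so 234 hypertensive women per group (468 in all). That means 468/0.16 = 2925 recruited, or 2925/0.85, about 3442, with attrition.

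Conversely, the difference detectable with 90% power from 2262 women after attrition is 3.2416 × SD × √(2/153.8): **14.8, 16.6 and 18.5 days** for SD 40, 45 and 50.

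**Step 5. Does simulating it change the answer?** A two-stage simulation of the first scenario (binomial number hypertensive, then normal times, t test) gave 81.6% without attrition and 74.2% with it, in line with the formula.

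**Step 6. Other readings of the first scenario.**
- 1131 already net of attrition: 181 per group, 81.4%.
- One-sided with no attrition: 88.7%, but this contradicts both the two-sided test and the stated attrition.
- A 2-df joint test of both parts of a two-part model, with equal hypertension rates: 73.1% without attrition and 64.4% with it.
- Skewed times (gamma or lognormal), 12 days, SD 40, 961 per group after attrition. The control-group mean is an assumption; the article gives none. These are simulated, with 4000 runs per cell:

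| Assumed mean | t test on days | Log-scale t test or rank test |
|---|---|---|
| 60 days | 74–76% | 92–98% |
| 80 days | 74% | 84–92% |
| 100 days | 74–75% | 79–88% |
| 120 days | 73–75% | 78–84% |

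A comparison of mean days stays near 75% whatever the shape. Only a different test, with a short enough mean, reaches 90%.

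**The case against.** The strongest reply is that the sample size was not derived from a two-sample formula. It came from a simulation on pilot data, and the planned analysis is a two-part model. A journal article commonly leaves simulation settings to the full protocol. With positive, skewed times and a log-scale or rank test, 90% is reachable with the same SD, difference, event rate and attrition if the mean is short enough. This stands: the unseen simulation cannot be ruled out as the source of the 90%. It shows only that 90% is possible, since it needs a mean and a test that the article does not state. The log-scale and rank tests also do not test a difference in mean days, which is how the article expresses the effect.

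A reader might also infer that the 362 is an error because it ignores attrition. The article does not support that. The figure is tied to women recruited and is correct as 16% of them. Women lost to follow-up can still become hypertensive, and the article plans notes review for them where possible. What is missing is the analysable number beside it.

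Finally, results will be reported with 95% confidence intervals, and 2262 is a minimum. Both limit the harm of a misread null result, but neither makes the power statement follow from its inputs.

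**Conclusion.** The point holds as a failure to reproduce. On the printed inputs, a two-sided comparison of mean days has about 75% power for 12 days at SD 40 after 15% attrition, and 81% with none. The other two scenarios give about 78% (84%) and 80% (86%). None delivers the stated power.

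This rests on three assumptions: the contrast is between mean days among hypertensive women, hypertension rates are equal in the two groups, and the 15% attrition removes hypertensive women in proportion.

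It would go too far to say that the trial's true power is 75%, or that the simulation is wrong. The simulation's distribution, mean and test are not shown, and under some assumed settings it could have produced 90%. What can be said is that a reader cannot get from the stated inputs to the stated power, and that the natural reading falls about 15 percentage points short.

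**What to change.** Check the R simulation against the printed inputs, then do one of the following.

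- **If it compared mean days:** restate the power as about 75% for 12 days at SD 40 (78% for 14 days at SD 45, 80% for 16 days at SD 50). Alternatively, keep 90% and restate the detectable differences as about 14.8, 16.6 and 18.5 days.
- **If it used a skewed distribution with a log-scale, rank or two-part test:** state the mean time, the distribution, the test and how attrition was applied. Express the target effect on the scale that was tested.

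In either case, keep 362 as the number expected among women recruited, and add that about 308 would be analysable after 15% attrition.

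The cost is wording, plus rerunning or rereading an existing simulation. The stated power may become less favourable. No extra recruitment and no change to the design or analysis is proposed.

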#### BP during hypertensive pregnancy

A sample size of 256 per group will be sufficient to detect a 5 mm Hg difference in systolic BP between groups, accounting for 15% attrition and an SD of 16 mm Hg, based on data from the BUMP pilot and PELICAN studies, inflated from 14 mm Hg because BUMP 2 will include hypertensive women from BUMP 1 and those with chronic or GH not previously randomised in BUMP 1.^6 14^ The sample size was calculated using NCSS PASS V.12.0.

Women randomised in BUMP 1 who develop hypertension will remain in their randomisation groups and move seamlessly into the BUMP 2 trial. This will occur automatically via the telemonitoring system and their inclusion in BUMP 2 assessed retrospectively. The precise numbers and proportion of women migrating from BUMP 1 to BUMP 2 will not be fixed. We will aim to recruit a minimum of 512 women directly into the BUMP 2 trial in addition to those that migrate in order to ensure adequate power: women who have CH or have developed GH and are not taking part in the BUMP 1 trial will be randomised to either usual care using clinic BP to guide treatment or BP self-monitoring with telemonitoring and automated feedback.

Both trials will be undertaken in approximately 15 maternity units in England to achieve the sample size in the anticipated time frame. Our previous pilot trial has confirmed that women and clinicians are willing to participate in this type of randomised controlled trial and we have used recruitment estimates from this trial, together with trial management experience and expertise of the coinvestigator group to inform strategies to meet the required target size.^6^

### Data management

An online clinical data management system will be used, with all clinical data entered directly onto the electronic case report forms (CRFs) and stored on a study-specific database. Paper backup forms will be available if the online database cannot be accessed. Data collected on paper forms will be entered on to the database at the earliest opportunity, by single data entry. Patient-completed questionnaires will be completed directly on to the system by the participant wherever possible, with manual single data entry of paper copies if required. Telemonitored mHealth data are stored on a centralised database, secured behind NHS firewalls, designed and maintained by the University of Oxford, Department of Engineering Science.

### Randomisation

Women who agree to participate in the trial (BUMP 1 or BUMP 2) will be randomised on a 1:1 ratio either to BP self-monitoring or usual care by the recruiting researcher. An independent statistician will generate a randomisation sequence list for each trial, using permutated varying blocks and stratified by recruitment site and parity. The generated schedules were then imported to the randomisation module within the online data management system for site to carry out the randomisation. Women will be randomised by the recruiting researcher using the online data management system. Women who develop hypertension during BUMP 1 and migrate to BUMP 2 will stay in their original randomisation group. A manual telephone based backup randomisation system will be used in the event the online system is not available.

### Statistical analysis

#### General consideration for both trials

The primary statistical analysis will be carried out on the basis of intention to treat (ITT). Thus, after randomisation participants will be analysed according to their allocated treatment group irrespective of what treatment they actually receive. We will endeavour to obtain full follow-up data on every participant to allow full ITT analysis, but we will inevitably experience the problem of missing data due to withdrawal, lost to follow-up, or non-response questionnaire items. The results from the trial will be prepared as comparative summary statistics (eg, difference in means) with 95% CIs. The study results will be reported in accordance with the Consolidated Standards of Reporting Trials 2010 statements and full detailed statistical analysis plans will be prepared before the final analysis by an independent statistician.

#### BP during higher risk pregnancy

The primary analysis will determine whether there is a difference in the time to diagnosis between the randomised groups (usual care vs self-monitoring) and will be performed using a two-part model, such as the hurdle model.^15^ The model takes into account participants who developed a raised BP or not and the time to raise BP, adjusting for stratification factors. This method has the advantage that all women who are recruited to BUMP 1 will contribute to the primary analysis. Continuous secondary outcomes, such as birth weight and length of stay, will be analysed by means of regression method adjusting for stratification factors. Binary secondary outcomes, such as the development of severe hypertension, development of any complications and stillbirth rate, will be analysed by means of a log binomial model.

#### BP during hypertensive pregnancy

An ITT analysis will include women recruited to BUMP 1 who become hypertensive and women recruited de novo to BUMP 2 with GH and CH analysed separately. The primary analysis for BUMP 2 will in each case compare BPs between the intervention and control groups. Analysis of the BP outcome will be by means of a linear mixed-effects model, which can accommodate data where participants have repeated measurements, and also accounts for missing data (assuming data are missing at random). Each of a participant’s BP measures will be modelled by means of a linear mixed-effects model, including random effects for participants and assuming an unstructured variance covariance matrix between measurements from the same participant. Time of BP measurement and randomised group, as well as their interaction term, will be included as fixed effects in the model. A fixed effect will also be included for whether the participant was from BUMP 1 or not in the GH analysis. As a sensitivity analysis inclusion from BUMP 1 or not will be tested as a moderator of the treatment effect. By means of appropriate contrasts, the difference in mean BP of participants in the randomised groups from both BUMP 1 and de novo recruitment will be compared.

BP load and area under the curve will be analysed as continuous outcomes by means of a linear regression model, adjusting for whether the participant originated from BUMP 1. Continuous secondary outcomes, such as birth weight and length of stay, will be analysed by means of regression model. Binary secondary outcomes, such as the development of severe hypertension, incidence of complications and incidence of stillbirth, will be analysed by means of a log binominal model.

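### The BUMP 2 primary model leaves out the stratification factors and a pre-randomisation systolic BP, and so gives up precision that costs almost nothing to recover

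*Protocol article*

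**What the plan says.** The Randomisation section says that an independent statistician prepares a list for each trial, "using permutated varying blocks and stratified by recruitment site and parity". Women who migrate from BUMP 1 to BUMP 2 keep their original allocation.

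For BUMP 1 (Statistical analysis, BP during higher risk pregnancy), the two-part primary model covers whether raised BP occurs and "the time to raise BP, adjusting for stratification factors". The continuous secondary outcomes of BUMP 1 are adjusted in the same way.

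For BUMP 2 (Statistical analysis, BP during hypertensive pregnancy), GH and CH are analysed separately with a linear mixed model. Its fixed effects are given as a list: "Time of BP measurement and randomised group, as well as their interaction term, will be included as fixed effects in the model". One more is added for the GH analysis only: whether the woman came from BUMP 1. The model for BP load and area under the curve adjusts for BUMP 1 origin alone. The other continuous secondary models name no covariate.

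Table 1 lists "Maternal demographics; including gestation, EDD and parity" at trial entry. It does not list a clinic BP there; clinic BPs come from the notes review.

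**The concern.** Two pieces of pre-randomisation information go unused in the stated BUMP 2 model, and they matter in different ways.

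- **Site and parity.** Stratifying balances the arms on these factors and so reduces the true variance of the treatment difference. A model without them does not credit that reduction. If the strata predict SBP, the reported standard error is too large, the interval too wide and the test conservative. The article makes this adjustment in one of its two linked trials and not in the other, and gives no reason.
- **Baseline SBP.** Earlier SBP can be expected to predict later SBP. Without it the standard error is valid for the unadjusted comparison but larger than it need be, and any chance difference between arms at entry stays in the estimate.

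The stakes are highest where numbers are smallest. The 512 is a single total, but the primary analysis splits GH from CH.

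**Working it through.** **Inputs from the article**

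- BUMP 2 size and target difference: "A sample size of 256 per group will be sufficient to detect a 5 mm Hg difference in systolic BP between groups".
- Variation and loss: "accounting for 15% attrition and an SD of 16 mm Hg".
- Allocation: women "will be randomised on a 1:1 ratio either to BP self-monitoring or usual care".
- Migrants: 16% of 2262, about 362 women.

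**Assumptions**

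- Power and significance level. The BUMP 2 sample size text states neither. I take the BUMP 1 terms, "with 90% power and 5% level of significance (two sided) and assuming a 15% attrition rate".
- Correlation r between baseline and follow-up SBP: 0.3 to 0.6.
- Size of the GH and CH groups: each holds half of the 512, for illustration.

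**Step 1. Reproduce the stated size.** n per arm = 2 (SD/δ)² (1.960 + 1.282)² = 2 × (16/5)² × 10.51 = 215.2, so 216. The exact t-test needs 217, and 217/0.85 = 255.3, so 256. The stated figure is reproduced as a plain unadjusted two-sample comparison. At 80% power it would have been 190, which supports the 90% assumption.

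**Step 2. Power without adjustment.** 256 × 0.85 = 217.6 per arm. SE = 16 × √(2/217.6) = 1.534. 5/1.534 − 1.960 = 1.300, so power is 90.3%.

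**Step 3. Power with baseline SBP.** Residual SD = 16 × √(1 − r²). The column for n needed uses the normal formula, divided by 0.85.

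| r | Residual SD (mm Hg) | n per arm for 90% | Power at 217.6 per arm | Power at 108.8 per arm |
|---|---|---|---|---|
| none | 16.0 | 255 | 90.3% | 63.5% |
| 0.3 | 15.3 | 231 | 92.7% | 67.6% |
| 0.4 | 14.7 | 213 | 94.5% | 71.1% |
| 0.5 | 13.9 | 191 | 96.4% | 75.9% |
| 0.6 | 12.8 | 163 | 98.3% | 82.2% |

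The last column is half of 217.6 per arm: a GH or CH group with half of the 512 and no migrants.

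**Step 4. GH with migrants.** 362/2 × 0.85 = 153.8 per arm from BUMP 1. Added to 108.8, this gives 262.6 per arm. SE = 16 × √(2/262.6) = 1.396. 5/1.396 − 1.960 = 1.62, so unadjusted power is about 95%.

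**Step 5. Strata.** The article gives no figure for how far site and parity predict SBP, so the gain from them cannot be quantified here. Its direction is known. The price is small: about 15 sites and one parity term against roughly 435 women (2 × 217.6).

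**The case against.** **The article is a summary and promises full analysis plans.** True, and a missing covariate list would be no finding. But this passage does give a list, detailed enough to name a covariate used in one population only, and the BUMP 1 passage mentions the strata. The difference between the two trials is in the text itself.

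**Baseline SBP may already be in the model as a response.** The outcome runs from baseline to delivery and each BP measure is modelled, so this is possible. Even so, the model has a free group term and states no constraint of equal means at baseline, so a chance imbalance at entry would still pass into the averaged contrast. The handling needs stating either way.

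**Adjusting for SBP at BUMP 2 entry could do harm.** This objection stands in full. A migrant's SBP at BUMP 2 entry is measured after she was randomised, at the point of detection that self-monitoring is meant to change. Conditioning on it could bias the GH comparison. Only a reading from before randomisation is safe.

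**The size is uncertain.** Also true. The correlation is assumed, and eligibility based on raised BP narrows the baseline range and may lower it. For migrants the usable reading is older, which may weaken it further.

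A reader might extend the point to BUMP 1, where gestational age at entry is not named, or to the questionnaire change outcomes, where a baseline score is not named. The article does not support either. The BUMP 1 model is an outline with no stated time origin and already adjusts for the strata. No model is specified for the change outcomes. Both can properly be settled in the analysis plan.

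**Conclusion.** The point holds for BUMP 2. The stated primary model omits the two factors that randomisation was stratified on, out of line with BUMP 1, and makes no stated use of SBP before randomisation as a covariate.

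The consequence is lost precision. A reader might infer that the treatment estimate is biased or the trial underpowered as a whole; neither follows. Randomisation protects the unadjusted estimate, and 256 per group reproduces without any adjustment.

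At an assumed r of 0.3 to 0.6, baseline adjustment is worth 9% to 36% of the sample size (r²). It matters most for a group that receives no migrants, such as CH, at about 64% unadjusted if it holds half of the 512. It matters least for GH, which may already be near 95% if the expected migrants arrive. These figures rest on the assumed correlation, a two-sided 5% test, 90% design power and the illustrative half split. The gain from the strata is additional and unquantified.

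**What to change.** State in the BUMP 2 analysis plan, before the analysis:

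1. Site and parity enter the primary mixed model for GH and for CH, and the continuous secondary models, as in BUMP 1. Both are fixed before randomisation for every woman, so this is safe for migrants too.
2. A clinic SBP from before randomisation, taken from the notes review, enters the primary model as a covariate. That reading is not also modelled as an outcome.
3. For women who came from BUMP 1, the reading is one from before their BUMP 1 randomisation, and SBP at BUMP 2 entry is not used as a covariate.
4. A rule says which reading counts as baseline and how a missing one is handled.

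Items 1 and 3 need wording only. Items 2 and 4 have a small cost: the notes review must identify a dated pre-randomisation reading, and some will be missing. No change to recruitment, visits or sample size is needed.
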